### Eligibility criteria {10}

#### Inclusion criteria

All consecutively admitted adult patients at risk of massive transfusion after severe trauma are screened for enrolment. Patients older than 18 years, admitted directly from the injury scene to a level-I trauma center, are eligible provided that they have two criteria: (1) a transfusion of at least one unit (U) of RBC prior to hospital admission or within the first hour after their admission (a delay of 90 min is tolerated if transfusion is decided within 1 h post admission) and (2) prediction by an assessment of blood consumption (ABC) score ≥ 2 [14] or by physician judgment of the need for a massive transfusion (defined by a transfusion of at least 10 RBC during the first 24 h or 3 RBC during the first hour).

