#### Relevant concomitant care permitted or prohibited during the trial {11d}

From admission, all patients are managed according to European recommendations. Briefly, the source of bleeding should be identified as soon as possible and treated with emergency surgery and/or embolization following standard practice [16]. Regarding resuscitation, patients are treated in both groups with restricted volume replacement strategy, early transfusion of blood products with a RBC:FFP ratio between 1:1 and 2:1. Tranexamic acid (TXA) is intravenously administered within 3h after injury at a loading dose of 1 g infused over 10 min followed by an intravenous infusion of 1 g over 8 h [17]. Fibrinogen concentrate is administered in case of fibrinogen concentration <1.5 g/L [18] or viscoelastic evidence of a functional fibrinogen deficiency [19]. Platelets are administered to maintain a platelet count above 50 x 10^9^/L. Vasopressors can be infused in addition to fluids to maintain target systolic arterial blood pressure (>90 mmHg or >110 mmHg for head-injured patients). Blood samples are regularly drawn from admission to test hemostasis (prothrombin time ratio, Quick time, fibrinogen concentration, and viscoelastic tests where available), blood electrolytes, hepatic and renal function, and blood gases.

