### Statistical methods

#### Statistical methods for primary and secondary outcomes {20a}

The risk of alpha error corresponds to a usual threshold: 5%. All our tests will be bilateral. The initial characteristics of the patients will be represented in a comparative table according to the two treatment groups. Quantitative and qualitative variables will be presented with the usual parameters, mean, and standard deviation as well as numbers and percentages.

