##### Analysis of the main outcome

The main outcome is the total blood consumption (RBC, FFP, and platelets). It will be analyzed after verification that the time spent in the study up to H24 is not significantly different between the two groups. If this duration is not different, the total number of units transfused over 24 h between the two groups will be compared using a bilateral student intent to treat *t* test (if the application conditions are not met, we will use a non-parametric Mann-Whitney *U* test). If the duration is different, the amount of blood products used per hour between the two groups will be compared using an intention-to-treat Student *t* test (= total number of bags transfused over 24 h divided by the time spent in research during the first 24 h), in order to control for an attrition bias created by patients who died before 24 h.

The per-protocol analysis will be performed on patients who actually received treatment within 1 h of admission to the hospital.

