## Discussion

The PROCOAG trial explores the management of post-traumatic coagulopathy using pro-thrombin concentrate complex (PCC) in addition to standard blood products and fibrinogen. As opposed to fresh frozen plasma, PCC is readily available at admission and we hypothesized that early correction of coagulation factor deficiency optimizes patient blood management and therefore reduces the total number of blood products transfused within the first 24 h after hospital admission.

Hemorrhage is a leading cause of death in patients with trauma. Although blood products remain the standard for treating hemorrhagic shock, they are a limited and perishable resource. Moreover, concerns are increasing that blood products exert an immunomodulatory effect and negatively affect clinical outcomes [24–26]. Resuscitation strategies that decrease the need for transfusions without increasing complications, therefore, would represent a clinically important innovation.

Eligibility criteria were determined to select patients with severe acute bleeding early in the process so that PCC can be early administrated in the trauma bay on patient arrival. The study hypothesis states an empiric administration of PCC may enhance clotting capacity and decrease total blood product consumption. In consequence, the investigators expect several patients may not require a massive transfusion. The effect of the study protocol on massive transfusion will be investigated in a planned subgroup analysis (see above).

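### Every branch of the primary comparison is unadjusted, so precision that pre-treatment bleeding-severity values could give is forgone; the test itself is valid and adequately powered as planned

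*Protocol article*

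**What the plan says.** The protocol article's section on the analysis of the main outcome sets out three branches, and none contains a baseline covariate:

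- If time in study up to 24 h does not differ between arms, total units "will be compared using a bilateral student intent to treat" t test.
- For data unsuited to the t test, "if the application conditions are not met, we will use a non-parametric Mann-Whitney" test.
- If time in study differs, "the amount of blood products used per hour between the two groups will be compared using an intention-to-treat Student" t test.

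The general statement under {20a} is "The risk of alpha error corresponds to a usual threshold: 5%. All our tests will be bilateral". Baseline data have only a descriptive use there: "The initial characteristics of the patients will be represented in a comparative table according to the two treatment groups".

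Other sections name information on bleeding severity that can exist before study drug. The inclusion criteria use "prediction by an assessment of blood consumption (ABC) score" of 2 or more, with physician judgment as the alternative, and accept red cells given either before admission or early after it. The concomitant-care section {11d} states "Blood samples are regularly drawn from admission to test hemostasis (prothrombin time ratio, Quick time, fibrinogen concentration" among other tests. The Discussion rests the trial on the idea that "early correction of coagulation factor deficiency optimizes patient blood management".

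**The concern.** Total units in this population will vary widely. The section on additional analyses accepts that some enrolled patients will not have massive bleeding, while others will receive 10 or more red-cell units. Part of that spread reflects how severely a patient was bleeding on arrival, which treatment cannot have influenced. An unadjusted test leaves that part in the residual. A model with well-chosen baseline values would remove some of it, narrow the interval for the treatment effect, and correct for chance imbalance in severity.

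The candidates are reasonable on the protocol's own terms. The ABC score is used at entry to predict massive transfusion. Pre-hospital red cells fall outside the endpoint, which counts from hospital admission. If factor deficiency drives blood use, the admission prothrombin ratio should predict the outcome. Units given between admission and study drug are a different matter, because they are part of the endpoint, and they are not proposed here.

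**Working it through.** **Inputs from the sample size section {14}:** 12 versus 9 units (difference 3), 162 per group, 80% power, two-sided alpha 0.05, 350 to be included after an allowance for loss. The section gives no SD and says only that units are not normally distributed. No section gives the share of outcome variance explained by any baseline value (R²), so R² below is an assumption.

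**Step 1: the plan's own figure.** Without an SD, 162 cannot be reproduced independently, only inverted:

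SD = 3 × √(162/2) / (1.960 + 0.842) = 27 / 2.802 = 9.64 (t test).

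With the Mann-Whitney efficiency of 3/π, the implied SD is about 9.42. A pure Poisson count would need only 2.802² × (12 + 9) / 3² = 18.3, so 19 per arm; that was not the basis.

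**Step 2: unadjusted precision.** SE = 9.64 × √(2/162) = 1.071 units. The 95% half-width is 1.96 × 1.071 = 2.10 units. Power = Φ(3/1.071 − 1.960) = Φ(0.842) = 80%, as it must be.

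**Step 3: adjusted precision.** The residual SD is 9.64 × √(1 − R²), and power = Φ(3 / (1.071 × √(1 − R²)) − 1.960).

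| Assumed R² | SE ratio | 95% half-width (units) | Power, 162 per arm |
|---|---|---|---|
| 0 | 1.000 | 2.10 | 80.0% |
| 0.05 | 0.975 | 2.05 | 82.0% |
| 0.10 | 0.949 | 1.99 | 84.0% |
| 0.20 | 0.894 | 1.88 | 88.0% |
| 0.30 | 0.837 | 1.76 | 91.8% |

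**Step 4: where in the range?** The protocol suggests caution about the upper rows. Entry selects on ABC score and early transfusion, which narrows their range. The section on additional analyses itself describes the ABC score as imperfectly accurate. Early deaths cap the units of some of the sickest patients, which weakens a linear relation between severity and units.

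**Step 5: the benchmark.** The table compares with a t test only. Since the protocol expects non-normal data, Mann-Whitney may be the operative test. Its power depends on a distribution shape that is not given. In simulations with means 12 and 9 and a pooled SD of about 9.6, it came out above the t test for lognormal data with a common coefficient of variation, and below it for negative-binomial data with a common dispersion. The gain over that branch therefore cannot be stated.

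**Step 6: are the covariates available?**

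- *Prothrombin ratio:* drawn from admission as part of care, but it is not an eligibility criterion. The hourly study visits in {13} follow treatment, and no section fixes a sample before study drug.
- *ABC score:* an alternative to physician judgment, so it is not shown to be recorded for everyone.
- *Pre-hospital red cells:* one way of meeting a criterion that early in-hospital units can also meet; a unit count is not shown to be recorded.

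**The case against.** The strongest reply is that nothing here is wrong. Randomisation makes a two-group test valid, and the trial was sized at 80% power for a plain comparison. Adjusted models are often left to an analysis plan, and one may exist. All of this stands, except that the last part does not remove the point: the article positively fixes the primary method, and the point concerns that choice.

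A reader might infer that the trial is underpowered or its primary result biased. The documents support neither: any power lost is relative to an optional model, not to the plan.

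A reader might also infer that all three covariates are entry measures already held for every patient, so that adjustment needs no new data. The documents do not show this (Step 6). It matters most for the prothrombin ratio, because a sample taken after study drug would be a post-treatment covariate and could absorb part of the effect.

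Nor can the gain be presented as a firm number of free patients, because it rests wholly on an assumed R².

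A further fair objection is that replacing only the 24 h total would leave out the units-per-hour branch, the plan's device for early deaths. The fix must cover it.

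**Conclusion.** The point holds as a missed efficiency, not as an error. The primary comparison is unadjusted in all three branches, while prognostic values that can precede study drug are likely to exist. Against a t test with the implied SD of about 9.6 and 162 per arm, adjustment would raise power from 80% to about 82, 84, 88 or 92% for R² of 0.05, 0.10, 0.20 or 0.30. These R² values are assumptions, and the lower ones deserve real weight. If R² is near zero, essentially nothing is gained or lost. The gain relative to Mann-Whitney is unknown. A model also gives something that no branch states: an estimate, with an interval, of the mean difference in units on which the trial was sized.

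**What to change.** Before unblinding, amend the section on the analysis of the main outcome as follows:

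- Make the primary intention-to-treat analysis a linear model of 24 h units on arm plus a short, fixed list of covariates. Use the same model for units per hour wherever that branch applies.
- Admit only covariates confirmed to be recorded before study drug: first admission prothrombin ratio, pre-hospital red-cell units, and ABC score where its components are captured.
- Use robust standard errors and simple imputation of missing baseline values, so that no randomised patient is dropped.
- Report the adjusted mean difference with its 95% CI, and keep the unadjusted comparison as supporting.

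The cost is slightly more analysis work and a check that these fields, with sampling times, are in the eCRF; no more patients are needed. The trade-off is reliance on a mean-based model for a skewed count. The covariate list must be settled without sight of results by arm, because a later choice would not be credible.

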##### Secondary outcome analysis

We will use the same strategy as for the primary endpoint in order to compare each quantity of RBC, FFP, and platelets, independently; i.e., a Student’s *t* test (if the application conditions are not met, we will use a non-parametric test).

Comparison by a Student’s *t* test (if the application conditions are not met, we will use a nonparametric test) of the values of the Quick Time between the two groups.

The delay between the time of the trauma and clinical hemorrhage control will be compared between the two randomization groups by a Student’s *t* test (if the application conditions are not met, we will use a nonparametric test).

The number of thromboembolic events at D28 will be recoded as a qualitative variable. At least one event (pulmonary embolism or deep vein thrombosis) will be required for this variable. It will then be compared using the chi^2^ test between the two groups (when the conditions for the application of the chi^2^ test are not met, the Fisher’s test will be used).

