**Methods:**

This is a prospective, randomized, multicenter, double-blind, parallel, controlled superiority trial. Eligible patients are trauma patients with major bleeding admitted to a French level-I trauma center. Patients randomized in the treatment arm receive 1 mL/kg (25 IU/ml of Factor IX/Kg) four-factor PCC within 1-h post-admission while patients randomized in the controlled group receive 1 mL/kg of saline solution 0.9% as a placebo. Treatments are given as soon as possible using syringe pumps (120 mL/h). The primary endpoint is the amount of blood products transfused in the first 24 h post-admission (including red blood cells, frozen fresh plasma, and platelets). The secondary endpoints are the amount of each blood product transfused in the first 24 h, time to achieve prothrombin time ratio < 1.5, time to hemostasis, number of thrombo-embolic events at 28 days, mortality at 24 h and 28 days, number of intensive care unit-free days, number of ventilator-free days, number of hospital-free days within the first 28 days, hospitalization status at day 28, Glasgow outcome scale extended for patients with brain lesions on initial cerebral imaging, and cost of each strategy at days 8 and 28. Inclusions have started in December 2017 and are expected to be complete by June 2021.

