#### Outcomes {12}

The primary outcome is the total number of blood products transfused within the first 24 h after hospital admission, including RBC, FFP, and platelets. The choice of this primary outcome is based on the following rationale. First, a recent randomized control trial exploring the effect of vasopressin use after severe trauma on the same endpoint [20], Second, even if transfusion is considered a pillar in the management of acute bleeding, blood products are associated with adverse events and poor clinical outcome [11, 21]. Third, mortality after severe trauma is a complex process depending on hemorrhage but also on traumatic brain injury and pre-existing medical conditions, specifically in elderly patients [22]. We thus believe that 24h total blood consumption is an accurate proxy of the severity of the bleeding until the hemorrhage stops.

Secondary outcome measures are (1) number of separate units (and volume) of RBC, FFP, and platelets and transfused in the first 24 h; (2) time to achieve prothrombin time ratio < 1.5; (3) time to hemostasis, defined as the time necessary to control bleeding in the surgical field (operative field is dry without further foreseeable homeostatic procedures) or to control contrast blush after embolization during an interventional radiology (no more dye flushing); (4) number of thrombo-embolic events at 28 days; (5) mortality at 24 h and 28 days; (6) intensive care unit (ICU)-free days (number of in-hospital days outside ICU) within the first 28 days; (7) ventilator-free days during ICU stay within the first 28 days; (8) hospital-free days within the first 28 days; (9) hospitalization status at day 28; (10) GOSE for patients with brain lesions on initial scan; and (11) cost of each strategy at days 8 and 28. Cost analyses will be performed on expensive care: blood products and procoagulant treatments administered, imaging exams, surgeries, and length of stay in each healthcare unit.

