#### Participant timeline {13}

All consecutive trauma patients admitted directly from the injury scene who require RBC transfusion with a risk of massive transfusion are screened on admission. Eligible patients are then rapidly enrolled by the study investigator. They should be randomized and treated accordingly within 60 min post-admission. After patient treatment, follow-up includes hourly visits until 6 h post-admission, as well as visits at 12 and 24 h to measure prothrombin ratio, assess hemorrhage control and monitor adverse events. Thrombo-embolic events are under special scrutiny during the entire hospital stay because they are frequently expected adverse effects of PCC treatment. Each suspicious thrombo-embolic event should be confirmed with venous Doppler echography or angiography and treated following standard practice. Thromboprophylaxis is left to physician discretion. Patients are followed for 28 days with the last visit aiming at collecting the Glasgow outcome scale extended (GOSE) for patients with brain lesions on initial cerebral imaging, mortality, and place of living (Fig. 1).

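### The secondary endpoint is the time until the prothrombin time ratio falls below 1.5, but the analysis section specifies a test on Quick Time values, so no test of the stated endpoint is specified

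*Protocol article*

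**What the plan says.** The Outcomes section lists as its second secondary outcome the "time to achieve prothrombin time ratio < 1.5". The abstract gives the same endpoint in the same position ("time to achieve prothrombin time ratio < 1.5, time to hemostasis"), and the Objectives section uses it as the definition of normalised hemostasis.

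The Participant timeline schedules the measurements that this endpoint needs: "hourly visits until 6 h post-admission, as well as visits at 12 and 24 h to measure prothrombin ratio".

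The Secondary outcome analysis section covers blood product quantities, then has one sentence on coagulation, then turns to hemorrhage control. The coagulation sentence opens "Comparison by a Student’s *t* test (if the application conditions are not met, we will use a nonparametric test" and gives the object of the comparison as the values "of the values of the Quick Time between the two groups" in the two groups. It names no threshold, no elapsed time and no sampling time.

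The section on concomitant care says that blood is drawn from admission to "test hemostasis (prothrombin time ratio, Quick time, fibrinogen concentration, and viscoelastic tests where available". Quick time and the prothrombin time ratio are separate items in that list.

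**The concern.** The endpoint is a time to an event: how long until the ratio first crosses 1.5. The analysis sentence compares a laboratory value. These are different variables, and a result for one does not answer the question put by the other.

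The endpoint matters to the trial's argument. The Discussion hypothesises that early correction of coagulation factor deficiency is what reduces transfusion, and this is the secondary endpoint that bears most directly on that step. With the variable and the sampling time both open, the comparison could be settled after the data are seen. Values also exist only for patients alive to be sampled, and the sentence says nothing about deaths or about patients who never reach the threshold.

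**Working it through.** The article gives no figure to reproduce here, so the check is a comparison of texts.

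1. **Definition.** The abstract, the Objectives and the Outcomes section agree: the variable is a duration that ends when the ratio drops below 1.5.

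2. **Analysis.** The Secondary outcome analysis follows the order of the Outcomes list. Items 1 to 4 of that list are blood products, time to ratio below 1.5, time to hemostasis and thromboembolic events. The analysis section runs blood products, Quick Time, hemorrhage control, thromboembolic events. The Quick Time sentence therefore stands in the place of item 2.

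3. **Same measure or not.** The concomitant care section lists the ratio and Quick time as two tests. Even if Quick Time were read as another name for the ratio, the sentence compares values, not times to a threshold.

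4. **Elsewhere in the statistical sections.** The general methods, main outcome, cost, interim, additional-analysis and missing-data sections contain no analysis of time to ratio below 1.5. The additional-analysis section says only that secondary outcomes will also be tested in the massive-transfusion population, without naming a variable or method for this one.

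5. **Can the endpoint be derived?** Yes. Hourly visits to 6 h give six measurements, and those at 12 h and 24 h make eight. The gaps between visits are 1 h up to hour 6, then 12 − 6 = 6 h and 24 − 12 = 12 h. A crossing is known only to lie between two visits, so its recorded time can be late by up to 1 h before hour 6, up to 6 h between hours 6 and 12, and up to 12 h after that.

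6. **Would a t test on the times do?** No. A patient who dies first, or who stays at 1.5 or above to 24 h, has no observed time. Dropping such patients conditions the comparison on an outcome that arises after randomisation. A patient already below 1.5 at the first sample has no crossing to time, and this can happen because the inclusion criteria require transfusion and predicted massive transfusion, not an abnormal ratio.

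7. **How the plan treats death elsewhere.** The main outcome analysis switches to a per-hour rate if time in study differs, so as to deal with deaths before 24 h. The cost analysis provides for censoring by death, and mortality is compared by Kaplan-Meier. This endpoint has no comparable provision.

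**The case against.** The strongest defence is loose wording. The sentence sits exactly where this endpoint belongs and may simply be a misworded reference to it. That is possible, and the text does not prove that a different endpoint was deliberately substituted. But the sentence speaks of values, and the article separates the two tests, so the passages need reconciling on either reading. Nor is this a detail left to a separate analysis plan: the article does name an analysis, but of another variable.

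Four stronger readings are tempting, and the documents do not support them:

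- **That the endpoint is lost or cannot be reported.** The serial ratio measurements are scheduled, so the times can be derived. What is missing is a prespecified test.
- **That the Quick Time comparison is biased in a known direction.** If early deaths differ by arm, a comparison limited to sampled survivors could favour the arm that loses its most coagulopathic patients. But no sampling time is named, an early sample would lose few patients, and the article gives no mortality or coagulopathy rate from which to size the effect. It is a risk, not a demonstrated bias.
- **That recorded times are generally late by 6 to 12 h.** This is the worst case, and only for crossings after hour 6. Clinical samples may narrow the gaps. The schedule is the same in both arms, so it costs precision; no differential bias is shown.
- **That a t test on the times is a second error.** The article does not state such a test for this endpoint. The point is a caution for the repair.

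**Conclusion.** The point holds as a contradiction within the current text: the endpoint is defined consistently in three places as a time to a threshold, and the only analysis offered in its place is of laboratory values at an unspecified time. No test of the stated endpoint is specified in this document.

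Its size is limited. It concerns one of eleven listed secondary outcomes, and the data needed are already scheduled. The amount of possible survivor bias cannot be estimated from what is given. The conclusion rests on reading Quick Time values as the article's own list of tests presents them, as a measure distinct from the ratio. Under the looser reading the variable would be right, but the named t test would still not suit it and the sentence would still need rewriting. The sponsor should correct it before unblinding; confidence in the mismatch is high.

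**What to change.** Replace the Quick Time sentence in the Secondary outcome analysis with an intention-to-treat time-to-event analysis of the first prothrombin time ratio below 1.5, up to 24 h. The text should state:

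- the time origin;
- that death before attainment is a competing event, and that patients alive and still at 1.5 or above are censored at 24 h;
- how visit spacing is handled: either attainment is assigned to the scheduled visit and analysed in discrete time, or an interval-censored method is used. A standard Gray test assumes right-censored times and does not by itself deal with intervals;
- how patients already below 1.5 at the first sample are treated.

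Present the patients at 1.5 or above on the admission sample, where one is available, as a supporting analysis only. The article does not explicitly schedule a ratio before randomisation, and it does not say what share of patients would qualify, so this subset should not become the main population. If Quick Time values are wanted, keep them as a separate descriptive outcome at named time points.

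The cost is a change of wording and slightly more analysis work, with no study visit added. Times after hour 6 will remain coarser than those before it.
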